#### Data Collection

We will collect demographics data at baseline. Data will be collected at 4 and 12 weeks. The 12-week time point will be considered the primary endpoint for the study. The AI platform on the smartphone app’s back end will provide patient analytics on the usage of the mobile app (ie, intake of medications in the app diary and access frequencies).

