#### Study Design

The study has a single-blind and sequentially randomized design. The full design of the study will include two arms with 2 (modality: app versus app with text) × 2 (format: an app with visualization versus an app with contextual medication text information) × 2 (context: contextual medication information versus information without context) + 1 (control: app) design. The design is depicted in Figure 1. The randomized trial using binary options (*yes* or *no*) provides the stratification needed to identify groups that are prone to get benefits from the different presentations of medication information. The results from the sequential randomized design will help us detect statistically significant differences using a larger sample size. The first randomization helps with filtering patients who have better information recall regardless of the app. The second randomization helps with finding the actual effects of the tool when compared with different interventions.

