**Figure 1 figure1:**
[figure not shown]
Study design. The participants are randomized first at R: one group uses only the app (A) and another group is given the app with medication information text (AT). At time point 1 (T1), after 4 weeks, both groups are evaluated for information recall (>80%). Then, after a second randomization (R), the participants are divided into the following groups: app with medication information text (AT), app with contextual medication information text (ACT), and app with visualization (AV). T0: baseline; T2: time point 2 (after 12 weeks).

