#### Study Subjects and Recruitment Methods

We will recruit patients (18-65 years of age) from our clinics. Inclusion criteria will include participants who have access to a smartphone, can provide their consent, do not have any cognitive impairment, and who have at least two medications on profile for which we have created a visualization. At the time of recruitment, we will ensure that the patients meet the minimum cutoff score of 34 during cognitive screening using the TICS-M test and health literacy level [32]. Eligible patients will be allocated in a 1:1 ratio to the two arms of the study according to a computer-generated random sequence stratified by third-party software.

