#### Procedure

In the first randomization, patients will be randomized into two groups at baseline. The control group (ie, the app-only [A] group) will have the smartphone app with no visualization, and the intervention group will have the app with text information only as in the current Medication Guide (AT) [43]. At 4 weeks, patients from both the control and intervention groups from both arms, who have scores of 80% or higher in the information recall survey, will continue in the study with the same intervention, in either the A or AT group. Those who do not meet the performance cutoff will be rerandomized further into two groups for each arm. In the second randomization at 4 weeks, the control group from the first arm (A) will have the smartphone app with just text information about medication (AT), and the intervention group will have the smartphone app with the prototype of medication information visualization (AV). The control group from the second arm (AT) will have the app with contextual medication information in a text format (ACT), and the intervention group will have the app with our visualization design (AV). This part of the study will continue for 8 weeks. The monitoring is not a continuous process. Only the principal investigator will have access to the main file and will check the adherence and patient analytics at 4 and 8 weeks.

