#### Survey Tools

Three survey measures will be used. The first survey will be used to understand information recall; we will design a timed questionnaire, with *true* or *false* responses, for each medication in a patient’s regimen that includes the 10 pieces of crucial medication information we embedded into the visualization interface. Each patient will be tested on different medications at 4 and 12 weeks to show understanding and knowledge. For example, if a patient takes simvastatin, metformin, and losartan, only those specific medication-related questions will be asked. The second survey will help us to understand the patient’s perception of medication knowledge. We will use a validated survey instrument to assess patients’ attitudes, confidence, and perceived medication knowledge [44]. This instrument was validated with high internal consistency (Cronbach α=.833). The third survey will use the 8-item Morisky Medication Adherence Scale (MMAS-8). The MMAS-8, whose scores range from 0 to 8 with lower scores indicating lower adherence, is a widely used tool for self-reported medication adherence; the scale was found to be reliable and significantly associated with adherence control (*P*<.05), with 93% sensitivity as well as 53% specificity for low adherence in a validation study [37].

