#### Sample Size Justifications

To detect a 1-point improvement on the Likert scale and 80% power at the 5% significance level, the study would require 100 subjects in each group with 1:1 allocation for the second randomization (ie, AT: AV and ACT: AV). To allow for an 11% loss due to dropouts and those lost to follow-up, we would need to recruit 888 patients, allowing up to 50% of the patients to move to the second randomization following the first randomization with a score of 80% or higher in the medication recall questionnaire survey with assigned intervention. Recruitment of 888 patients is also sufficient to detect a 1-point improvement on the MMAS-8 (the secondary outcome), with 80% power at 5% significance. Therefore, our target is to recruit 900 patients.

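### Aim 3 schedules no outcome before the first randomization, so A versus AT has no baseline score to adjust for and the week-4 recall filter cannot be read as independent of the app

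*Protocol article*

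**What the plan says.** All places are in Aim 3 of the protocol article.

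- **Data Collection:** "We will collect demographics data at baseline. Data will be collected at 4 and 12 weeks". Week 12 is the primary endpoint.
- **Survey Tools:** for recall, "Each patient will be tested on different medications at 4 and 12 weeks to show understanding and knowledge". No time points are given there for the perception survey or the MMAS-8.
- **Study Subjects and Recruitment Methods:** the only scores obtained before entry are a "minimum cutoff score of 34 during cognitive screening using the TICS-M test and health literacy level". Neither is a trial outcome. Patients must be people "who have at least two medications on profile for which we have created a visualization"; unlike in Aim 1, no newly started medication is required.
- **Procedure:** "In the first randomization, patients will be randomized into two groups at baseline", to A or AT. At week 4, patients scoring 80% or more on recall stay on their assignment. The others are rerandomized, to AT or AV (visualization) in the first arm and to ACT (contextual text) or AV in the second.
- **Figure 1 caption:** T0 is defined as baseline, but no measurement is attached to it.
- **Study Design:** "The first randomization helps with filtering patients who have better information recall regardless of the app".
- **Sample Size Justifications:** the size is set "To detect a 1-point improvement on the Likert scale", and likewise for one point on the MMAS-8.

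**The concern.** Every outcome is first observed after four weeks of exposure to an assigned condition. This has four consequences.

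1. The Study Design section describes the week-4 split as finding patients whose recall is good whatever the app does. That property could be seen only before exposure. At week 4, a patient who already knew the information and one who learned it from A or AT look the same.
2. The A versus AT comparison has no pre-treatment value of any outcome, either to check balance or to gain precision. It is a real comparison in this plan: patients are allocated 1:1 to these two arms, and Data Analysis provides for tests between arms.
3. Change from study entry in comprehension or adherence cannot be stated. Patients who pass at week 4 are never rerandomized, so they have no pre-treatment score at any stage.
4. Patients lost before week 4 can be described by demographics and screening results only.

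A starting score that was not collected cannot be recovered after enrolment.

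**Working it through.** **1. The schedule.** Data Collection names demographics at baseline and data at weeks 4 and 12. Survey Tools puts recall at weeks 4 and 12. Recruitment adds only the TICS-M and health literacy. No section places recall, perception or the MMAS-8 before the first randomization.

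**2. The plan's own sample size.** Inputs from Sample Size Justifications are 100 per group, four second-stage groups, 11% loss and 50% moving on.

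- 4 × 100 = 400, and 400 × 1.11 / 0.50 = 888, as stated.
- Dividing by 0.89 instead gives 400 / 0.89 / 0.50 = 899, within the target of 900.
- No standard deviation (SD) is given. With a two-sided 5% test (assumed), 80% power and a difference of 1, the 100 per group implies SD = 1 / [(1.96 + 0.842) × √(2/100)] ≈ 2.52.

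**3. Does the missing baseline bias the randomized comparisons?** This was simulated with 20,000 trials of 100 per group, SD 2.52 and an unmeasured prior level correlated with the outcome.

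| Correlation of prior level with outcome | Bias (points) | Type I error | Power for 1 point |
|---|---|---|---|
| 0.5 | −0.002 | 4.9% | 80% |
| 0.8 | −0.0004 | 4.95% | 79% |

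There is no bias and the error rate holds.

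**4. What precision is forgone?** Adjusting for a baseline score with correlation r to the outcome leaves a variance of SD² × (1 − r²), so the share removed is r². For A versus AT, with 900 / 2 = 450 per arm and no loss assumed, the standard error in SD units is √(2/450) × √(1 − r²). The last column scales the plan's 100 per group by 1 − r² (rounded up at the implied SD) to show the same gain on a familiar footing. The correlations are assumptions.

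| r | Variance removed | SE, A versus AT (SD units) | Equivalent of 100 per group |
|---|---|---|---|
| 0 | 0% | 0.067 | 100 |
| 0.3 | 9% | 0.064 | 91 |
| 0.5 | 25% | 0.058 | 75 |
| 0.7 | 49% | 0.048 | 51 |

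**5. What can the week-4 filter not show?** Take a pass rate of 50%, the complement of the share the plan moves on. Suppose a share p0 of all patients would already score 80% or more at T0 and still pass. The fraction of passers who met the cutoff before exposure is then p0 / 0.50. For p0 = 10%, 20% or 30% this is 20%, 40% or 60%. The p0 values are illustrative; the article gives none, and the planned data could not tell these cases apart.

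**The case against.** The strongest reply is that randomization already does the work. A reader might infer from the missing T0 scores that the trial cannot separate prior knowledge or adherence from the effect of an intervention. The documents do not support that. A versus AT, AT versus AV and ACT versus AV are all randomized, so prior level is balanced in expectation, and the simulation agrees. The effect of having any app at all cannot be identified, but that is because every group has one, and T0 scores alone would not cure it.

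Second, the contrasts that are sized are those after the second randomization, and week-4 scores can serve as their baseline. This stands. For recall the week-4 score is an imperfect covariate, since different medications are tested at the two times and only patients below 80% enter.

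Third, a reader might take "To detect a 1-point improvement on the Likert scale" to promise a change from entry. Data Analysis compares means between groups and names no change score, so a between-group difference is the natural reading. The wording needs clarifying, but it is not a contradiction.

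Fourth, the week-4 rule can be applied without T0 data. This also stands: what fails is the interpretation given to the rule, not the rule.

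Fifth, a T0 recall test has real drawbacks. It could raise the week-4 pass rate, on which the recruitment figure depends. A patient with only the required two medications would have to be tested on one of them again. Both objections are sound and shape the fix.

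Finally, the article may condense a fuller protocol, Figure 1 is not visible, and the baseline sentence does not contain the word only. The schedule is nevertheless stated outright, and nothing else in the article contradicts it. Demographics, TICS-M and health literacy could be used as covariates, but none is a baseline value of an outcome.

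**Conclusion.** The point holds in a limited form. As scheduled, no outcome precedes the first randomization. The randomized comparisons remain valid. The consequences are:

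- no baseline outcome for adjusting A versus AT;
- no estimate of change from entry;
- no starting scores for early losses or for patients who pass at week 4;
- a week-4 recall filter that cannot carry the meaning Study Design gives it.

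The loss in precision is 9%, 25% or 49% of outcome variance at assumed correlations of 0.3, 0.5 or 0.7. The share of passers who already met the cutoff at entry is unknown and would stay unknown. This is a matter of precision and interpretation. It is worth correcting because the remedy is cheap and is available only before enrolment.

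**What to change.** 1. **Data Collection.** Revise to: *Demographics, the MMAS-8 and the perception survey will be completed at T0, before the first randomization. The outcome surveys will be completed at 4 and 12 weeks, those at week 4 before any rerandomization.*
2. **Data Analysis.** Use each T0 score as a covariate for the corresponding outcome in the A versus AT comparison. Week-4 scores can serve for AT versus AV and ACT versus AV.
3. **Study Design.** Delete the last four words of "The first randomization helps with filtering patients who have better information recall regardless of the app", and describe the split as recall after four weeks on the assigned condition.
4. **Sample Size Justifications.** State that improvement means a between-group difference.
5. **Recall at T0.** Treat as optional. If it is added, give no feedback on answers, say which medications will be reused, and reconsider the assumed 50% pass rate. Without it, the recall component still has no T0 value, and item 3 becomes essential.

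The cost is one more electronic administration of two questionnaires the trial already uses, a few minutes per patient, plus the text changes.

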#### Study Measures

The following study measures will be conducted:

Medication information comprehension from the first survey (primary outcome) [45]; the comprehension measure will be a composite of three subscales:Relevance to understanding patients’ attitudes,Patients’ levels of confidence and knowledge of medication use, measured using a Likert scale, andInformation recall subscale, measured using a dichotomous scale (ie, true or false).Survey on patients’ perceptions of medication information.Medication adherence (secondary outcome) will be operationalized by the following:MMAS-8 [46] survey score; the dichotomous response categories are yes or no for each item, andAnalytics of the patients’ daily intake of medications diary from the smartphone app.

#### Data Analysis

Demographic information will be presented using descriptive statistics. We will analyze the groups using *t* tests to detect differences between the means for continuous data. Chi-square analysis will be used to evaluate differences between arms for primary and secondary outcomes. We will use the univariate analysis of variance to calculate the mean differences between groups. If the distribution is not normal, we will use general linear modeling for the data analysis [47,48]. The AI-based analytics data from the smartphone will show us the patients' medication intake and we will correlate that score with our interventions.

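### The second-stage contrasts are compared without using the week-4 scores taken before re-randomisation, which costs precision but causes no bias

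*Protocol article*

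**What the plan says.** The protocol article, Aim 3, Data Analysis, names four methods:

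- for scores treated as continuous, *t* "tests to detect differences between the means for continuous data";
- a method tied by name to the trial's outcomes: "Chi-square analysis will be used to evaluate differences between arms for primary and secondary outcomes";
- a univariate analysis of variance, for mean differences among the groups;
- a fallback: "If the distribution is not normal, we will use general linear modeling for the data analysis".

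No covariate, change score or repeated-measures term appears with any of them.

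On timing, Data Collection says "We will collect demographics data at baseline. Data will be collected at 4 and 12 weeks", and makes week 12 the primary time point. Procedure and the Figure 1 caption place the recall assessment at week 4, ahead of the second randomisation: patients below 80% are re-randomised, and the others stay on their first assignment. Sample Size Justifications asks for 100 patients in each group of that second randomisation, for AT against AV and ACT against AV.

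**The concern.** Whether a score counts as a baseline depends on which randomisation the contrast comes from. At enrolment the plan states only that demographics are collected ("We will collect demographics data at baseline"), so A versus AT has no stated outcome baseline. The second-stage contrasts differ. Patients have already been scored on recall when they are re-randomised, so the later assignment cannot have affected that score, and it measures one component of the primary outcome.

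The analysis section does not use it. It brings in a general linear model only when the data are not normal, whereas the useful reason to model here is a prognostic score measured before randomisation. At stake is precision in the contrasts on which the trial is sized. The Aim 3 Limitations section itself concedes that the study would lack rigor if about 888 patients could not be recruited, so precision available without further patients has value.

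**Working it through.** **Reproducing the plan's total.** Inputs from Sample Size Justifications: 100 per group, four groups (AT and AV from arm A; ACT and AV from arm AT), 50% reaching the second randomisation, 11% loss.

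- 4 × 100 = 400; 400 / 0.50 = 800; 800 × 1.11 = 888, the stated figure.
- Dividing by 0.89 gives 899, close to the target of 900.

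**Effect size behind 100 per group.** No SD is given, so the 100 cannot be checked directly. Solving backwards for 80% power at two-sided 5% (sidedness is not stated; two-sided is assumed), unadjusted:

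- normal approximation: d = (1.960 + 0.842) × √(2/100) = 0.396, so a 1-point difference implies an SD of 1/0.396 = 2.52;
- with the *t* distribution: d = 0.398.

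**Effect of adjustment.** Let r be the correlation between the week-4 and week-12 scores among re-randomised patients. ANCOVA multiplies the residual variance by 1 − r². The effective sample size is then 100/(1 − r²) per group, and the standardised effect is 0.398/√(1 − r²). The protocol gives no r, so a range is shown.

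| r | 1 − r² | Effective n per group | Power at 100 per group | n per group for 80% power |
|---|---|---|---|---|
| 0 | 1.00 | 100 | 80% | 100 |
| 0.3 | 0.91 | 110 | 83.6% | 91 |
| 0.5 | 0.75 | 133 | 89.9% | 75 |
| 0.6 | 0.64 | 156 | 93.8% | 64 |

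**Allowing for selection on recall.** Everyone re-randomised scored below 80% on recall, which narrows the range of that covariate. Assume bivariate normal scores and a cutoff that removes the upper half, in line with the protocol's 50%. The covariate's variance then falls to v = 1 − 2/π = 0.363 of its full value, and the correlation becomes r√v / √(1 − r² + r²v). The SD among re-randomised patients is kept at the value implied by 100 per group.

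| Full-range r | r after selection | Effective n per group | Power at 100 per group |
|---|---|---|---|
| 0.3 | 0.19 | 104 | 81% |
| 0.5 | 0.33 | 112 | 84% |
| 0.6 | 0.41 | 120 | 87% |

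Perception and MMAS-8 scores are narrowed only through their correlation with recall, so their loss is smaller than this.

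**The case against.** The strongest reply is that covariates belong in a statistical analysis plan, which is not shown. The article never says that its tests are unadjusted, univariate means one dependent variable, and general linear modelling can carry covariates. This stands in part: a fuller plan may already adjust. But the section is not silent. It names the methods and reserves modelling for non-normal data, so the point concerns the method chosen and not a missing detail.

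It is also fair that the trial is sized at 100 per group for 80% power, which fits an unadjusted test. Nothing here shows the trial to be underpowered or the analysis invalid.

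Three stronger readings are tempting, and the protocol does not support them.

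- **All three surveys are established week-4 baselines.** Only recall is explicitly placed before re-randomisation. For perception and MMAS-8 this is inferred from the general statement in Data Collection. The primary outcome is a composite, and no week-4 composite is described.
- **The analysis ignores the randomisation strata.** The phrase "according to a computer-generated random sequence stratified by third-party software" describes the first 1:1 allocation to the two arms and names no factors. The second randomisation is not described as stratified.
- **Recall is tested on different drugs at the two visits.** Survey Tools says "Each patient will be tested on different medications at 4 and 12 weeks to show understanding and knowledge". The example that follows, and the statement that questions cover each medication in the regimen, fit better with questions that differ between patients. A clarifying sentence would help. If the literal reading were meant, r would probably be lower, but adjustment would remain valid.

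**Conclusion.** The point holds as one of efficiency. For AT versus AV and ACT versus AV, the stated analysis leaves unused a score measured before the relevant randomisation. The unadjusted comparison is unbiased under randomisation.

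The gain depends on a correlation that the protocol does not give. Power would rise from 80% to about 84%, 90% or 94% if r is 0.3, 0.5 or 0.6 among re-randomised patients. For recall it would rise only to about 81%, 84% or 87% if those are full-range values and the cutoff removes the upper half. These figures also assume a two-sided 5% test, 100 analysed per group and a linear relation between the two scores. If r were zero, the loss would be one degree of freedom. The change is worth making because it costs almost nothing; the trial does not fail without it.

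**What to change.** State that each second-stage contrast of a continuous week-12 score is analysed by ANCOVA, with randomised group and the week-4 value of the same score as terms. If no week-4 composite exists, use week-4 recall as the covariate for the primary outcome. Do the same for MMAS-8 if it is measured at week 4, and say in Data Collection which surveys are taken at that visit and that they precede the second randomisation.

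Do not adjust the first-stage A versus AT comparison for week-4 scores. They come after that randomisation and may be affected by it.

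Add a sentence in Survey Tools on whether the medications tested differ between patients or between visits.

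The cost is one model statement and one degree of freedom per contrast. If the surveys are taken at week 4 as Data Collection implies, no new visit or measurement is needed.

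### Aim 3 names chi-square for outcomes that are numeric scores sized on 1-point improvements, and its fallback for non-normal data is the same normal-error model

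*Protocol article*

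**What the plan says.** All references are to Aim 3 of the protocol article.

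- **Data Analysis** makes four statements about method. On continuous data: "We will analyze the groups using *t* tests to detect differences between the means for continuous data". On the trial outcomes by name: "Chi-square analysis will be used to evaluate differences between arms for primary and secondary outcomes". On group means: "We will use the univariate analysis of variance to calculate the mean differences between groups". On departures from normality: "If the distribution is not normal, we will use general linear modeling for the data analysis". It gives no cut-point or categories for the chi-square.
- **Study Measures** defines the primary outcome as a score: "the comprehension measure will be a composite of three subscales". The subscales mix Likert and true/false items.
- **Survey Tools** describes the secondary outcome: "The MMAS-8, whose scores range from 0 to 8 with lower scores indicating lower adherence".
- **Sample Size Justifications** sizes the primary comparison in points: "To detect a 1-point improvement on the Likert scale and 80% power at the 5% significance level". This gives 100 per group for AT against AV and for ACT against AV. It makes the same 1-point, 80% power claim for MMAS-8.
- **Data Collection** sets 12 weeks as the primary endpoint.

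**The concern.** The only test tied by name to the primary and secondary outcomes is one for categories. Neither outcome is defined as a category, and the study is not sized on a difference in proportions. A statistician who followed the sentence literally would have to cut each score at a point the article does not give, or cross-tabulate every score value and ignore the ordering. Either way, information that the sample size relies on is lost.

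The fallback is a lesser problem of the same kind. Bounded scores such as percent correct or 0–8 may well look non-normal, so the switch could be triggered. It would lead back to the model that had just been rejected.

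**Working it through.** **Inputs.** From Sample Size Justifications: 1-point difference, 80% power, 5% level, 100 per group, 1:1 allocation, two contrasts, 11% loss, 50% reaching the second randomisation. Not stated: SD, one- or two-sided test, any cut-point. Assumed below: two-sided test, normal score.

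**1. The plan's own figure.** Two contrasts of two groups give 4 × 100 = 400. Then 400 × 1.11 / 0.5 = 888, which matches. The 100 per group cannot be reproduced without an SD, so it is solved backwards from the two-mean formula:

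n = 2 (SD/δ)² (1.960 + 0.842)²

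100 = 2 × SD² × 7.849, so SD = 2.52 and d = 1/2.52 = 0.396. With the t distribution instead of the normal, d = 0.398. (One-sided, the implied SD would be 2.84.)

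**2. The same effect tested on a split score.** Let p0 be the control proportion above the cut. Then

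p1 = Φ(Φ⁻¹(p0) + d), h = 2 arcsin√p1 − 2 arcsin√p0, power = Φ(h√(n/2) − 1.960).

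Example with p0 = 0.40 and d = 0.398: Φ⁻¹(0.40) = −0.253, so p1 = Φ(0.145) = 0.558. Then h = 0.317, and 0.317 × √50 = 2.24. Power = Φ(2.24 − 1.96) = Φ(0.28) = 61%.

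| Control above cut | Treated above cut | Power, 100 per group |
|---|---|---|
| 10% | 19% | 44% |
| 20% | 33% | 55% |
| 30% | 45% | 59% |
| 40% | 56% | 61% |
| 50% | 65% | 60% |
| 60% | 74% | 58% |
| 70% | 82% | 53% |
| 80% | 89% | 45% |
| 90% | 95% | 31% |

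The pooled-variance formula with d = 0.396 gives nearly the same figures (60% at best, 30% at the 90% cut). By that formula, regaining 80% needs about 158 per group at the best cut and 375 at the 90% cut.

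**3. Chi-square without a split.** An unordered chi-square on a score in 3, 5 or 9 equally filled categories, at d = 0.396, has about 59%, 53% and 43% power.

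**4. Dependence on the SD.** If the true SD were 2.0, the mean comparison would have 94% power at 100 per group; at 3.0 it would have 65%. The absolute loss from splitting varies with this, but the split test remains the less efficient one under a normal shift.

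**5. The fallback.** With two groups, the t test, one-way ANOVA and a linear model with a group term are one model. On a simulated, rounded and bounded 0–8 data set (100 per group), all three gave p = 0.0088. As to harm: in null simulations of rounded, capped 0–8 scores (100 per group, 20,000 runs), with 16% to 58% of patients at the ceiling, the t test's type I error stayed between 4.8% and 5.2%.

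**The case against.** The strongest reply is that this is a condensed article listing familiar tools: t tests for two groups, ANOVA for several, chi-square for categorical results. The outcomes do have categorical parts, namely true/false recall items, yes/no MMAS-8 items and the 80% recall threshold at 4 weeks. A cut-point, and the choice of one primary test, are commonly left to an analysis plan that is not shown. The word general may also be a slip for generalized.

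Much of this limits the point, and three stronger readings should be resisted:

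- *That the trial will miss its 80% power.* The documents do not say that either total score will be split, and they give no SD. The loss is conditional.
- *That three tests are expressly assigned to the same outcomes, leaving a free choice.* Only chi-square names the outcomes. That the t test and ANOVA also cover them is an inference, though the sizing in points supports it.
- *That MMAS-8 differences would shrink to 0.93 + 0.53 − 1 = 0.46 of their true size.* The instrument is described "with 93% sensitivity as well as 53% specificity for low adherence in a validation study", but no split at low adherence is planned. The figures describe the questionnaire, and analysing the 0–8 score would not remove its measurement error either.

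What the reply does not answer is the text itself. Chi-square is assigned to the outcomes by name, and the 80% threshold is a re-randomisation rule at 4 weeks, not a 12-week endpoint. The fallback as worded gives no error distribution or link that would make it a generalized model. Detail in an analysis plan would not make either sentence correct.

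**Conclusion.** The point holds in limited form. The test named for the primary and secondary outcomes contradicts the basis on which the study was sized. If it were the deciding test on a split score, 80% power would fall to about 61% at best and to about 31% to 55% at cuts that leave 10%, 20%, 70%, 80% or 90% of controls above. This assumes an effect of about 0.40 SD solved from 100 per group, a two-sided 5% test, a normal shift, and a cut that the article never defines. The non-normality fallback is redundant as written, with little practical harm at 100 per group. The mismatch between test and sizing carries most of the weight.

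**What to change.** In the Aim 3 Data Analysis section:

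1. Name one primary analysis: a mean comparison (linear model or t test) of the 12-week numeric comprehension score within each second-randomisation contrast, AT against AV and ACT against AV.
2. Analyse MMAS-8 as its 0–8 score by the same method.
3. Keep chi-square for categorical variables only.
4. Delete the normality-triggered switch. Use inference that does not need normality, such as heteroscedasticity-robust standard errors or bootstrap confidence intervals.

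A binomial model for the recall counts is an optional sensitivity analysis.

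The cost is wording in the protocol and in any analysis plan. Recruitment, visits and data collection do not change. The change should be made before unblinded outcome data are seen.
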